### Safety outcomes

2.6

Safety outcomes will include the adverse events related to regional nerve blockade, such as allergic reactions, total spinal anesthesia, severe hypotension, malignant arrhythmias, and cardiac arrest, as well as postoperative complications including urinary retention, puncture site infection, pulmonary infection, deep vein thrombosis, pulmonary embolism, and atelectasis. All adverse events will be recorded and assessed throughout the study period.

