### Anesthetic and study interventions

2.8

All patients will fast for at least 8 h and refrain from clear fluids for at least 4 h prior to surgery. In the operating room, following the establishment of peripheral intravenous access, patients will receive oxygen via face mask at 5 L/min and undergo continuous monitoring of vital signs, including non-invasive blood pressure, percutaneous arterial oxygen saturation (SpO₂), heart rate, respiratory rate, and bispectral index (BIS). Under aseptic conditions, a radial arterial catheter will be inserted for continuous invasive arterial pressure monitoring. Anesthesia induction will be performed using propofol (2 mg/kg), sufentanil (0.5 μg/kg), and rocuronium (0.6 mg/kg). After induction of anesthesia, adequate topical anesthesia of the larynx and upper trachea will be achieved using lidocaine. Following preoxygenation, a double-lumen endobronchial tube will be placed. Correct positioning and depth of the double-lumen tube will be confirmed before initiating mechanical ventilation. The patient will then be repositioned into the lateral decubitus position with the surgical side uppermost.

A single senior anesthesiologist will perform ultrasound-guided thoracic paravertebral blocks under sterile conditions for all patients in groups L and R. The target injection levels are T4 and T6. For group L, under real-time ultrasound guidance and after confirming correct needle tip position, 10 mL of liposomal bupivacaine (133 mg/20 mL) (21) will be injected at each of the T4 and T6 levels according to a standardized technique, for a total volume of 20 mL. For group R, under identical ultrasound-guided and aseptic conditions, 10 mL of ropivacaine (0.5%) will be injected at each of the T4 and T6 levels, for a total of 20 mL. Patients in group P will not receive any nerve block. Following surgery, patient-controlled intravenous analgesia (PCIA) will be prepared for patients in groups R and P, but not for those in group L. Each PCIA pump will be prepared with a total volume of 100 mL, containing sufentanil and 8 mg of ondansetron. The total sufentanil dose will be calculated as 2 μg per kilogram of body weight. The background infusion will be set at a rate of 0.04 μg/kg/h. Additionally, the PCIA protocol will be configured with a bolus dose of 0.04 μg/kg and a lockout interval of 15 min to ensure medication safety.

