Study interventions									
Liposomal bupivacaine			×						
Ropivacaine & PCIA			×						
PCIA			×						
Outcome assessment									
QoR-15						×	×	×	
Pain-free interval				×	×	×	×	×	
VAS for pain at rest				×	×	×	×	×	
VAS for pain during cough				×	×	×	×	×	
Maximum VAS for pain						×	×	×	
First rescue analgesia				×	×	×	×	×	
Times of rescue analgesia				×	×	×	×	×	
Opioid consumption			×						×
NRS for anxiety						×	×	×	
NRS for sleep quality						×	×	×	
Analgesic Satisfaction									×
Incidence of PONV						×	×	×	
Severity of PONV						×	×	×	
Times of rescue antiemetic						×	×	×	
Confidence in coughing						×	×	×	
Confidence in ambulation						×	×	×	
Pneumothorax									×
Hemothorax									×
Drainage volume									×
Length of hospital stay									×
Adverse events									
Allergic			×	×	×	×	×	×	×
Total spinal anesthesia			×	×	×	×	×	×	×
Hypotension			×	×	×	×	×	×	×
Malignant arrhythmias			×	×	×	×	×	×	×
Cardiac arrest			×	×	×	×	×	×	×
Urinary retention			×	×	×	×	×	×	×
Puncture site infection			×	×	×	×	×	×	×
Pulmonary infection			×	×	×	×	×	×	××
Deep vein thrombosis			×	×	×	×	×	×	×
Pulmonary embolism			×	×	×	×	×	×	×
Atelectasis			×	×	×	×	×	×	×

According to SPIRIT, statement of defining standard protocol items for clinical trials.

Pre-op, preoperative; Intra-op, intraoperative; Post-op, postoperative; QoR-15, quality of recovery-15 scale; VAS, visual analogue scale; NRS, numerical rating scale; PCIA, patient-controlled intravenous analgesia pump; PONV, postoperative nausea and vomiting.

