### Statistical analysis

2.11

The normality of continuous variables will be assessed using the Shapiro–Wilk test. Data following a normal distribution will be reported as mean (standard deviation, SD), while non-normally distributed data will be presented as median (interquartile range, IQR). Binomial variables will be expressed as proportions. The correlation structure will be selected based on the quasi-likelihood under the independence model criterion (QIC). Data distribution will determine the use of either a normal or gamma distribution with identity or log-link functions. The primary hypothesis of this study is that group L can demonstrate a superior quality of postoperative recovery compared to both control groups, with the difference being both statistically and clinically significant. A generalized estimating equation (GEE) model will be used to analyze repeated measures of continuous variables accounting for within-subject correlations. Continuous variables measured at a single time point will be analyzed using *t*-tests or Mann–Whitney U tests depending on normality and categorical data will be analyzed using the χ^2^ test. Post-hoc pairwise comparisons are strictly contingent on a significant overall between-group difference and *p*-values are adjusted using the Bonferroni method and set at 0.017. For longitudinal outcomes, this correction governs testing at both the individual time-point and overall treatment effect levels, ensuring robust control of the type I error rate. Statistical significance will be defined as *p* < 0.05.

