All study outcomes will be analyzed in the modified intentiontotreat (mITT) population, including all patients who are randomized, received the assigned intervention, and completed all or part of the postoperative follow-up assessments. Patients will be included in the analysis according to their original allocation. To evaluate the robustness of the primary outcome and its sensitivity to protocol deviations, a per-protocol (PP) analysis will be performed as a sensitivity analysis to verify the reliability of the findings from the intention-to-treat analysis. Multiple testing correction will be applied to primary and secondary outcome measures where applicable. As a theoretical principle, this adjustment is generally not applied to safety indicators. Odds ratios (OR) and corresponding 95% confidence intervals (CI) will be reported where appropriate. No interim analysis will be planned. Missing data will not be imputed. Statistical analyses will be performed using SPSS (version 25.0; IBM SPSS). A two-sided *p*-value < 0.05 will indicate statistical significance, except where false discovery rate (FDR) corrections apply.

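### Safety is analysed in the same mITT set as efficacy, so a patient who dies or withdraws after an intraoperative harm and before any postoperative check leaves the safety comparison together with the event (minor)

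*Protocol article*

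**What the plan says.** Section 2.11 of the protocol article names one analysis set for everything: "All study outcomes will be analyzed in the modified intentiontotreat (mITT) population". Patients enter it on three conditions, "including all patients who are randomized, received the assigned intervention, and completed all or part of the postoperative follow-up assessments", and are then analysed as allocated. No separate safety set is named. The only analysis rule specific to safety is that multiplicity correction is generally not applied to it. On methods, the section says that "categorical data will be analyzed using the" chi-square test and that "Odds ratios (OR) and corresponding 95% confidence intervals (CI) will be reported where appropriate".

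Section 2.6 lists, as safety outcomes, harms related to the block, "such as allergic reactions, total spinal anesthesia, severe hypotension, malignant arrhythmias, and cardiac arrest", together with postoperative complications. It adds that "All adverse events will be recorded and assessed throughout the study period". In Table 1 (Section 2.9), rows such as "Total spinal anesthesia" and cardiac arrest are ticked from the intraoperative column onward. The first postoperative column is 6 h. Section 2.9 also requires serious adverse events to reach the DMC within 24 hours.

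**The concern.** Membership of a safety denominator should not depend on what happens after the harm. Here it does. The third mITT condition is met only by a patient who is still alive and in the study at a postoperative assessment, whereas the harms of most interest can occur in the operating room. A fatal intraoperative event, or one followed at once by full withdrawal, therefore removes its own patient from the comparison.

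The second condition adds two possible routes, depending on how receipt of the assigned intervention is read. A block stopped part-way because of a harm may not count as received. In group R the intervention is block plus patient-controlled intravenous analgesia (PCIA), and PCIA follows surgery, so an R patient whose block harm prevented PCIA might be dropped as well.

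At stake is the between-arm safety table. The article's Conclusion promises evidence on safety as well as efficacy. If the excluded event is the only one of its type, the comparison shows none.

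**Working it through.** **1. Does the mITT sentence cover safety?** It refers to all study outcomes, and Section 2.6 defines safety outcomes as outcomes of this study. No other text overrides it. It therefore covers them.

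**2. Who falls out?** Setting the entry conditions (Section 2.11) against the timing of treatment (Section 2.8) and of assessments (Table 1):

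| Situation | Assigned intervention received? | Some postoperative follow-up? | In the mITT set? |
|---|---|---|---|
| L, block completed, intraoperative harm, still in the study at 6 h | yes | yes | yes |
| L, block completed, intraoperative harm, dead or fully withdrawn before 6 h | yes | no | **no** |
| L or R, block abandoned because of a harm, followed up | depends on reading | yes | depends on reading |
| R, block given, PCIA never started because of a harm, followed up | depends on reading | yes | depends on reading |
| P, fatal intraoperative cardiac arrest | no (PCIA follows surgery) | no | **no** |

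The table assumes that the 6 h checks in Table 1 count as postoperative follow-up assessments, which is the reading most favourable to the plan. Exclusion is then certain only for death or full withdrawal before 6 h. It can occur in any arm, although a block harm can arise only in L and R, so the direction of bias cannot be derived.

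**3. What does one exclusion do to the reported figure?**

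- Arm size: Section 2.10 inflates 48 evaluable patients for 10% attrition. 48/(1 − 0.10) = 53.3, rounded up to 54, as stated.
- Event count: the article gives no event rate. One event in one arm is an assumption, used only to show the mechanism.
- With the patient kept: 1/54 = 1.9%. The exact (Clopper-Pearson) 95% lower limit is 1 − 0.975^(1/54) = 0.0005, or 0.05%. The upper limit solves (1 − p)^54 + 54p(1 − p)^53 = 0.025, giving 9.9%.
- With the patient excluded: 0/53 = 0%. The upper limit is 1 − 0.025^(1/53) = 0.067, or 6.7%.

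The event leaves the numerator and the patient leaves the denominator.

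**4. Does a test decision change?** No. With a single event in three arms of 54, the event is equally likely under the null hypothesis to fall in any arm, so an exact test gives p = 1. After the exclusion there is no event to test. Neither analysis would reject.

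**The case against.** The strongest reply is that the rule will almost never bite. Partial follow-up is enough, and Table 1 schedules adverse-event checks at 6, 12, 24, 48 and 72 h and at discharge. A patient who survives a cardiac arrest but is too ill for a questionnaire still has entries and stays in. That leaves death, or full withdrawal by someone just out of general anesthesia, within a few hours. This stands, and it is why the point is minor.

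A second reply is that the event is not hidden. It is recorded, it reaches the DMC within 24 hours if serious, and the Discussion commits the trial to CONSORT. This also stands. A reader might infer that a fatal event would go unreported, but the documents do not support that. What they omit is any text that returns the excluded patient to the between-arm comparison.

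A third reply is that a safety set is commonly defined in a statistical analysis plan, and Section 2.9 refers to a predefined plan that is not shown. This holds for the exact meaning of receiving the intervention, so the abandoned-block and missing-PCIA routes remain conditional. It does not hold for the main point. The article does not leave the safety population open but assigns it to the mITT set, and a separate safety set elsewhere would contradict that sentence.

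Three further inferences are tempting and should not be drawn:

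- *The exclusion destroys a usable test or odds ratio.* An odds ratio for 1/54 against 0/54 already has a zero cell, and a chi-square test would rest on an expected count of 1/3 per arm.
- *The excluded patients always carry the gravest events.* That fits deaths but does not follow for withdrawals.
- *The rule favours liposomal bupivacaine.* No direction can be derived.

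**Conclusion.** The point holds as a minor one. As written, Section 2.11 lets an intraoperative harm remove its own patient from the between-arm safety comparison when death or full withdrawal comes before the first postoperative check. In the illustration, one such case changes an arm's result from 1.9% to 0% and lowers its upper confidence limit from 9.9% to 6.7%.

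This rests on two assumptions. The event count is invented for illustration, because the article gives neither event nor exclusion rates, so no probability of omission can be stated. The 6 h checks are taken as postoperative follow-up assessments. The abandoned-block and missing-PCIA cases add to the problem only if the intervention is then read as not received. The defect is confined to the safety comparison. Adverse-event recording and DMC reporting are intact.

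**What to change.** In Section 2.11, limit the mITT sentence to efficacy outcomes and add wording to this effect: *Safety outcomes will be analysed by allocated group in every randomized patient in whom anesthesia was induced, with no condition on completing the assigned intervention or on postoperative follow-up.*

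Induction is a suitable entry point because it is common to all arms: Section 2.8 states "Anesthesia induction will be performed using propofol" and other agents before it separates the groups. Study treatment, by contrast, starts during the operation in L and R but only after surgery in P. Deleting the follow-up condition alone would not be enough, because a P patient who died during surgery, and possibly a patient with an abandoned block, would still fail the receipt condition.

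An induction-based set also counts events that precede the block. A supporting table of block-related events by block actually attempted, partial blocks included, would separate these, but it is optional.

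The cost is a few words and one more analysis set. No new data, visits or patients are needed, because Table 1 already records adverse events from the intraoperative period. Safety and efficacy denominators may differ by a few patients, and the report should say so. Where a patient withdraws fully and also restricts use of their data, the change may recover little, so its main gain is for deaths.

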### Patient and public involvement

2.12

Patients and the public will not participate in the study’s design, recruitment, conduct, or reporting. Study results will be shared with participants via email.

## Discussion

3

This prospective, open-label, randomized controlled trial plans to enroll 162 adult patients at our center. It is designed to evaluate the effect of a single ultrasound-guided paravertebral block using liposomal bupivacaine on postoperative recovery quality compared to conventional opioid-dependent intravenous analgesia and an established high-quality multimodal analgesia protocol. The trial will be conducted in accordance with the Consolidated Standards of Reporting Trials (CONSORT) guidelines. In addition to assessing overall recovery quality, the study will address three key clinical questions: whether the intervention provides sufficient baseline analgesia; whether it independently meets current standards for comprehensive pain management; and whether it confers significant clinical benefits beyond analgesia. The primary outcome is the overall quality of recovery, as measured by QoR-15 score at 24, 48, and 72 h after surgery. Secondary outcomes include multiple pain management quality assessments (such as pain-free interval and pain scores under various conditions), total consumption of sufentanil during surgery and hospitalization, anxiety and sleep quality scores at 24, 48, and 72 h postoperatively, the incidence and severity of PONV along with the use of rescue antiemetics at the same intervals, and patient confidence in coughing and ambulation assessed using an NRS. All postoperative evaluations will be performed daily at 17:00 until 3 days after surgery. Additional recorded outcomes include the incidence of pneumothorax or hemothorax, total postoperative drainage volume, and length of hospital stay.

The distinctive feature of the group L in this trial is its independence from both indwelling catheters and opioid reliance, representing a key divergence from conventional analgesic strategies. This approach may demonstrate advantages by circumventing drawbacks associated with catheter placement and opioid dependence. The primary objective of this design is to directly evaluate the impact of a single-injection thoracic paravertebral block using liposomal bupivacaine on the quality of postoperative recovery, with particular emphasis on the quality of postoperative pain management provided by this strategy. The three-arm trial design enables comparison across two distinct dimensions. The first comparator is the most fundamental opioid-dependent PCIA, representing baseline postoperative pain management. When administered within safe dosing parameters, PCIA can meet essential analgesic requirements for pain relief. The second comparator combines PCIA with a ropivacaine-based thoracic paravertebral block, constituting a more advanced pain management protocol designed to achieve comprehensive analgesia. This experimental design addresses two fundamental questions: whether the single-injection thoracic PVB using liposomal bupivacaine can fulfill the basic requirements of postoperative pain management, and what level of analgesic efficacy it can provide.

Conventional analgesic agents, including intravenous analgesics and local anesthetics, have half-lives insufficient to cover the entire postoperative recovery period. As a result, catheter-based techniques—such as continuous epidural, intravenous, or regional nerve block analgesia—remain widely used in postoperative pain management, despite introducing risks and inconveniences related to catheter placement. Liposomal bupivacaine represents a novel long-acting, sustained-release local anesthetic. The drug is encapsulated within multivesicular phospholipid vesicles, enabling controlled and prolonged release of bupivacaine. Pharmacodynamically, peak plasma concentrations are typically achieved within 30 min after local injection, with analgesic effects lasting up to 72 h (20). Notably, ERAS guidelines emphasize that postoperative analgesia should be initiated preemptively—before pain onset—and maintained effectively (24). Therefore, liposomal bupivacaine emerges as a promising option that may potentially revolutionize postoperative pain management paradigms.

The analgesic efficacy and sustained duration of liposomal bupivacaine have been demonstrated in clinical settings. A study involving local infiltration after hemorrhoidectomy showed that patients receiving liposomal bupivacaine experienced a median time of 14.2 h before requiring supplemental analgesia, compared to only 1.2 h in the control group—reflecting both its potent analgesic effect and significantly prolonged duration of action (25). When used for bilateral transversus abdominis plane (TAP) blocks following cesarean delivery, liposomal bupivacaine significantly enhanced the quality of postpartum recovery and markedly reduced postoperative opioid consumption (26, 27). Furthermore, this strategy provided a complete pain-free period of at least 15 h post-surgery (26). Regarding safety, multiple studies have reported no signs of local anesthetic systemic toxicity (LAST) associated with the local application of liposomal bupivacaine. Importantly, research in obstetric populations confirmed that plasma concentrations of bupivacaine remained within safe limits for both mothers and newborns (28). Therefore, liposomal bupivacaine exhibits a highly favorable safety profile when administered via local infiltration.

PVB is recommended as the preferred analgesic technique for video-assisted thoracoscopic surgery (VATS) in prospective guidelines, owing to its demonstrated advantage (7). PVB has been associated with lower incidences of hypotension and urinary retention compared to epidural analgesia, and the puncture pain associated with PVB is also significantly lower than that of the epidural route (19). Moreover, due to its technical characteristics, PVB can be administered unilaterally according to the specific surgical site. And, compared to PCIA that utilizes opioids, PVB has been shown to markedly reduce the incidence of PONV (29, 30). It also significantly decreases the frequency of postoperative emergency analgesia demands and the opioid consumption (30).

As recommended by clinical guidelines (24, 31, 32), postoperative analgesia should follow an opioid-sparing strategy, which is also a key advantage of multimodal analgesia. This approach not only improves the quality of pain control but also reduces opioid-related adverse effects. The aim of this prospective randomized controlled trial is to combine paravertebral block (PVB) technique with liposomal bupivacaine to investigate the impact of a single-injection ultrasound-guided PVB using liposomal bupivacaine on the quality of postoperative recovery. No placebo control for the purpose of balancing interventions will be included, so as to directly reflect the true clinical effect and value of this strategy. Furthermore, among the secondary outcomes, we plan to specifically analyze the postoperative analgesic quality of this strategy and its contribution to reducing adverse effects such as nausea and vomiting, thereby comprehensively evaluating the clinical significance of this catheter-free and opioid-sparing postoperative pain management approach. By comparing with two reference groups—patients receiving PCIA alone and those receiving PCIA combined with ropivacaine-based PVB—this study will assess the extent of improvement in postoperative recovery quality achievable with ultrasound-guided single-injection PVB using liposomal bupivacaine. Our hypothesis posits that a catheter- and opioid-free pain management strategy—enabled by the sustained-release profile of liposomal bupivacaine and high-precision ultrasound-guided thoracic paravertebral blockade—can provide effective analgesia after thoracic surgery. This RCT will help advance the transformation of pain management paradigms in real-world clinical practice.

